### Data collection and management

2.9

The participants will come to the outpatient clinic for follow-up visits every month for related audiology examinations and tinnitus scale assessments, and 1 or 2 assistants will collect and record the entire data. Personal information about potential participants and registered participants will be collected, shared and stored in an independent storage room to protect confidentiality before, during and after the test.

The access to the database will be restricted to the researchers in this study team.

### Statistical analysis

2.10

SPSS Version 25.0 (Chicago, IL) is utilized to analyze the age, course of disease, characteristics of tinnitus, THI, VAS score results, and mean value of tinnitus loudness in each group. The measurement data is expressed by $\bar{x}\pm s$. The independent sample *t* test is used for comparing the 2 groups. The Chi-Squared test is used for the composition ratio analysis of tinnitus severity and the difference in curative effect, and the compatibility design data rank sum test and analysis of variance are used for comparison within the group. If *P* is less than .05, the difference will be statistically significant.

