### Sample size

2.3

The calculation of the sample size is based on the visual analogue scale (VAS) score results. According to the pre-test results, the average score of the experimental group is estimated to be 3.1 and the standard deviation is 1.3. The control group average score is 4.2 and the standard deviation is 1.9. The sample size calculation formula is as follows:$$n=n1=n2=\frac{{\left(u_{a}+u_{\beta }\right)}^{2}\times \sigma^{2}}{\delta^{2}}\times 2$$

At the 5% significance level, a total of 38 patients are required for each group to achieve 80% power. The estimated withdrawal rate is 20%, and 48 patients will be included in each group.

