### Study design

2.5

Eligible participants are randomly assigned to the treatment group or the control group at a ratio of 1:1 using a random tool based on the central network.^[14]^ Randomization is performed without any stratification and generated by an independent statistician who is not involved in trial implementation or statistical analysis using SAS 9.3 software (SAS Institute, Cary, NC, USA). The clinical research coordinator enter the participant information on the tablet, and is given a random number. The research assistant gets the participants assignment from the computer. Throughout the research process, the research assistant is responsible for screening, recruiting participants, and assigning random number to the included participants. The result assessor is responsible for the assessment of the scale. All of the doctors, researchers, research assistants, participants, intervention supervisors, and statisticians, the grouping of personnel are unknowable.

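### Section 2.10 puts baseline variables under the same between-group tests at P<.05 as the outcomes; describe them without tests and use the baseline scores in the treatment comparison

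*Protocol article*

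**What the plan says.** Section 2.10 (Statistical analysis) opens with one list of variables: the software is "utilized to analyze the age, course of disease, characteristics of tinnitus, THI, VAS score results", followed by tinnitus loudness. Age and disease course are baseline variables; THI, VAS and loudness are outcomes that also have baseline values. Tinnitus characteristics are not itemised.

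The section then gives one method for measurement data: the independent-sample t "test is used for comparing the 2 groups". For categorical data, "The Chi-Squared test is used for the composition ratio analysis of tinnitus severity and the difference in curative effect". A single decision rule closes the section: if P "is less than .05, the difference will be statistically significant". Neither the t test nor the rule is limited to outcomes, and no sentence says that baseline variables are only described.

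Section 2.5 (Study design) says that participants are "randomly assigned to the treatment group or the control group at a ratio of 1:1 using a random tool based on the central network", and that "Randomization is performed without any stratification". Neither between-group method named in 2.10 uses a covariate.

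**The concern.** Age and disease course are fixed before allocation. In arms formed by a sound random process, any difference in them is due to chance by design. A significance test then addresses a hypothesis already known to be true, and every significant result is a false positive. A report that follows the rule as written could tell readers that the randomised groups differ when nothing but chance is at work.

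The test is also a poor guide to whether an imbalance matters. That depends on the size of the imbalance and on how strongly the variable is related to outcome, and the P value measures neither. In a trial of this size a sizeable imbalance can give P>.05. What is at stake is how the baseline table is read, and some precision that the stated analysis leaves unused. The type I error of the treatment comparison is not at stake.

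**Working it through.** **Inputs from section 2.3 (Sample size).** VAS mean 3.1 (SD 1.3) against 4.2 (SD 1.9), so the planned difference is 1.1. There are 38 per arm after withdrawal and 48 per arm enrolled. Pooled SD = sqrt((1.3² + 1.9²)/2) = 1.628.

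**The plan's own figures.** With these inputs, two-sided 5% and 80% power, the printed formula gives 35 per arm, or 36 with a t correction. The stated 38 is slightly conservative. Allowing for 20% withdrawal, 38/0.8 = 47.5, rounded up to 48, as stated. This point does not dispute the sample size.

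**Step 1: chance of a false baseline difference.** With k independent tests at .05, the probability of at least one is 1 − 0.95^k.
- k = 3: 1 − 0.95³ = 14.3%
- k = 6: 1 − 0.95⁶ = 26.5%

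Both counts are assumptions, because tinnitus characteristics are not itemised. The second adds baseline THI, VAS and loudness. These measure related things, so treating them as independent probably overstates that figure.

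**Step 2: the largest imbalance that passes the test.** In SD units it is t(.975, 2n−2) × sqrt(2/n), taking the test as two-sided (2.10 does not state sidedness).
- n = 38: 0.457 SD
- n = 48: 0.405 SD

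**Step 3: what an imbalance does to an unadjusted VAS difference.** Shift = rho × imbalance × 1.628, where rho is the correlation of the baseline variable with final VAS. The document gives no rho; 0.3 to 0.7 is assumed.

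| Imbalance at 38 per arm | rho 0.3 | rho 0.5 | rho 0.7 |
|---|---|---|---|
| Boundary, 0.457 SD | 0.22 points (20% of 1.1) | 0.37 (34%) | 0.52 (47%) |
| Median absolute, about 0.155 SD | 0.08 (7%) | 0.13 (11%) | 0.18 (16%) |

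The median is 0.6745 × sqrt(2/38) = 0.155 SD. The first row is a boundary case: chance alone exceeds it only 5% of the time.

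**Step 4: comparison with sampling error.** The standard error of the unadjusted VAS difference is 1.628 × sqrt(2/38) = 0.37. The boundary shifts of 0.22 to 0.52 are therefore about 0.6 to 1.4 standard errors, a variation the t test already allows for. In a simulation with no treatment effect, its overall rejection rate stayed at 5% for each rho.

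**Step 5: what adjustment would gain.** ANCOVA reduces the residual SD to 1.628 × sqrt(1 − rho²). By the normal approximation, ignoring the lost degrees of freedom, power at 38 per arm goes from 83.8% unadjusted to 87.0%, 92.5% and 98.5% for rho 0.3, 0.5 and 0.7.

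**The case against.** No sentence says that age or disease course is t-tested between arms. The list is of variables to be analysed in each group, and the next sentence gives mean and SD, which would also fit a descriptive table. This stands in part: the testing is implied by an open list followed by an unrestricted test and rule. It remains the natural reading, because nothing marks the baseline variables as exempt.

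A reader might infer that the plan will take P>.05 as proof that the arms are comparable. The document does not support that. It never calls the arms balanced or comparable, and it attaches no decision to a non-significant baseline test.

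A reader might also infer that the VAS result is likely to be distorted by 20% to 47% of the planned effect. That does not hold either. Those figures put the imbalance exactly at the significance boundary and rest on assumed correlations; at the median imbalance the share is about 7% to 16%. After randomisation the unadjusted comparison is unbiased, and its standard error covers chance imbalance.

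Finally, this is a condensed article, and covariate choice is commonly left to an analysis plan that is not shown. That is fair: the absence of a covariate list, like the absence of stratification, is not an error here. Adjustment is offered as an improvement on the t test that the article does state. The document does not show age or disease course to be prognostic, so the baseline score is the better-motivated covariate.

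**Conclusion.** The point holds as a minor one. On its natural reading, section 2.10 tests pre-randomisation variables between randomised arms at P<.05, where a significant result can only be chance. At least one such result has a probability of about 14%, assuming three independent tests and sound randomisation. A non-significant result would not establish balance, because differences up to about 0.46 SD at 38 per arm (0.41 SD at 48) escape a two-sided test. The treatment comparison remains valid; the loss is in interpretation and in unused baseline information. No sample size or planned effect changes.

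**What to change.** In section 2.10:
1. Separate baseline variables from outcomes. Report age, disease course, tinnitus characteristics and baseline scores by arm descriptively, without P values.
2. Limit the P<.05 rule to treatment-effect comparisons.
3. Replace the unadjusted between-arm t test for VAS and THI with ANCOVA adjusted for pre-specified baseline values: first the baseline score of the outcome being analysed, optionally age and disease course, whatever balance is observed. Section 2.8 already relies on before-and-after VAS and on THI decreases, so the baseline scores are being collected.

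The cost is one or two sentences and one to three degrees of freedom, with no extra patients or data.

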### Intervention

2.7

Therapy group:

1.Music intervention: Distribute customized players with left and right sound channels and over-ear headphones to patients, instruct patients to choose a comfortable loudness and focus on listening in an environment without external sound interference. Continuous or intermittent listening is not less than 2 hours a day for 3 consecutive months.2.Acupuncture intervention: the patient takes an appropriate position, fully exposes the surgical site, and locally disinfects the acupuncture site (Ermen, Tinggong, Tinghui, Yifeng, Zhongzhu, Xiaxi, Hegu, Taichong. Take the affected side), an acupuncturist with a Chinese medicine practice license and at least 3 years of clinical experience will perform acupuncture operations.

The acupuncture technique is stimulated for 10 seconds to achieve a sense of “deqi”. The needle is retained for 30 minutes, 3 times a week. The course of treatment lasts 3 months.

The control group will be treated with acupuncture alone, and the treatment plan will be the same as that of the treatment group.

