### Evaluation criteria and efficacy judgment

2.8

1.Tinnitus handicap inventory (THI)^[16]^: The THI scale is divided into 5 levels based on the total score. Grade I: Mildly affects life (0–16 points); Grade II: Slightly affects life (18–36 points); Grade III: Moderately affects life (38–56 points); Grade IV: Severely affects life (58–76 points); Grade V: Extremely affects life (78–100 points). The higher the grade, the more serious the degree of tinnitus. Those with a THI score of above 38 are considered moderate and severe tinnitus patients. Efficacy criteria:1.Cure: THI score dropped to less than 16 points;2.Significantly effective: THI score decreased value ≥17 points;3.Invalid: THI score decreased by <17 points, or even increased.^[17]^2.The visual analogue scale (VAS) marker scale is increased from 0 to 10 points one by one. It is up to the patient to judge the tinnitus loudness and the corresponding tinnitus influence expression map. The higher the score, the greater the tinnitus loudness and its influence. The larger is used to compare the changes in tinnitus loudness values before and after treatment for each patient.3.Adverse reactions: Including intolerance during treatment, dizziness caused by acupuncture, etc.

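### The between-group t test on VAS and THI makes no adjustment for baseline, although baseline and monthly scores are collected; ANCOVA or, better, a repeated-measures mixed model would add power at no data cost

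*Protocol article*

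**What the plan says.** Section 2.10 (Statistical analysis) lists THI and VAS among the variables analysed and states: "The independent sample *t* test is used for comparing the 2 groups". Analysis of variance does appear, but for another purpose: "rank sum test and analysis of variance are used for comparison within the group". Neither a covariate nor a between-group longitudinal model is mentioned.

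Other sections show which data will exist:

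- Section 2.8 uses the VAS to "compare the changes in tinnitus loudness values before and after treatment for each patient" and defines THI response by the fall in score, so pre-treatment values are needed for both scales.
- Section 2.9 schedules "follow-up visits every month for related audiology examinations and tinnitus scale assessments". VAS and THI are the only tinnitus scales that section 2.8 defines.
- Section 2.7: "The course of treatment lasts 3 months". Monthly visits therefore give up to three post-baseline scores per patient.
- Section 2.5: "Randomization is performed without any stratification".
- Section 2.3 sizes the trial on mean VAS scores of 3.1 (SD 1.3) and 4.2 (SD 1.9), with 38 per group for 80% power at the 5% level. It then adds: "The estimated withdrawal rate is 20%, and 48 patients will be included in each group".

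**The concern.** The t test takes one number per patient and has no term for where that patient started. Eligibility sets no VAS or THI range and randomisation is unstratified, so baseline severity can vary widely within groups and differ by chance between them. If baseline predicts outcome, a test on final scores leaves that explained variation in the error term. A test on change scores uses baseline, but with a fixed weight of one, which is too much when the correlation is low.

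The article does not say which of the two is meant. Section 2.3 reads like final scores and section 2.8 speaks of changes, and their power differs. Baseline adjustment removes the ambiguity: with baseline in the model, final score and change score give the same treatment estimate.

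What is at stake is precision that the planned data would already support, plus the use of the scores that patients provide before withdrawing.

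**Working it through.** **Inputs.** From section 2.3: means 3.1 and 4.2, so δ = 1.1; SDs 1.3 and 1.9; 38 per group; 5% level; 80% power; 20% withdrawal; 48 enrolled per group. Assumed: a two-sided test (the section does not say), the same SD at baseline and at the end, and a baseline-final correlation r of 0.3, 0.5 or 0.7, with r = 0 as the limiting case. The documents give no value for r.

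**1. The plan's own figure.** Root-mean-square SD: σ = √[(1.3² + 1.9²)/2] = √2.65 = 1.628. The printed formula gives n = 2(1.960 + 0.842)² × 2.65/1.1² = 34.4, so 35; the exact t calculation gives 36. The stated 38 follows if the SD is taken as 1.7 (37.5, rounded up). It is thus slightly conservative against σ = 1.628. Withdrawal: 38/0.80 = 47.5, so 48, as stated.

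**2. t test on final scores, 38 per group.** SE = 1.628 × √(2/38) = 0.373. Noncentrality = 1.1/0.373 = 2.945 on 74 degrees of freedom. Power = 83%.

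**3. Alternatives.** The effective SD is σ√(1 − r²) for ANCOVA and σ√[2(1 − r)] for a t test on change. Power from the noncentral t, two-sided 5%:

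| r | ANCOVA SD | ANCOVA power | Change SD | Change-score t test power | Final-score t test power |
|---|---|---|---|---|---|
| 0 | 1.628 | 83% | 2.302 | 54% | 83% |
| 0.3 | 1.553 | 86% | 1.926 | 69% | 83% |
| 0.5 | 1.410 | 92% | 1.628 | 83% | 83% |
| 0.7 | 1.163 | 98% | 1.261 | 96% | 83% |

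Taking one degree of freedom for the covariate does not alter the ANCOVA percentages. At r = 0.5, 38 patients per group act like 38/(1 − 0.25) = 50.7.

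The ordering does not depend on the chosen r. 1 − r² never exceeds 1, and 1 − r² = (1 − r)(1 + r) never exceeds 2(1 − r). Apart from that one degree of freedom, ANCOVA is therefore at least as precise as either t test.

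**4. Withdrawal, as a check on direction only.** A simulation used 48 per arm, baseline plus three monthly scores, SD 1.628, equal correlations, a true month-3 difference of −1.10 and 4,000 replicates.

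- About 20% dropout, completely at random: every method was unbiased. At r = 0.3, 0.5 and 0.7 the SEs were 0.369, 0.375 and 0.366 (completer t test on final scores), 0.357, 0.327 and 0.260 (completer ANCOVA), and 0.356, 0.322 and 0.258 (repeated-measures likelihood).
- About 21% dropout driven by the last observed score, in opposite directions in the two arms (a deliberately adverse invention): mean estimates were −1.30 to −1.54 for the completer t test, −1.19 to −1.22 for completer ANCOVA, and about −1.10 for the repeated-measures likelihood.

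**The case against.** The strongest reply is that nothing is broken. Under 1:1 randomisation the t test is valid, and on final scores it exceeds the planned 80% power. A chance baseline difference is not bias, because its variation is already in the test's standard error; unstratified allocation is no defect either. The gain depends on a correlation that nobody has stated, and at 0.3 it is only three percentage points over final scores. All of this stands, and it makes the point one of efficiency.

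Three stronger readings are tempting, and the article does not support them.

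- *The plan ignores baseline altogether.* Section 2.8 speaks of changes and classifies THI response partly by its decrease, and section 2.10 does not exclude a t test on change scores. What can be said is that no baseline covariate is named.
- *The t test will be a month-3 analysis of completers, biased by a known amount.* Section 2.10 gives no time point, analysis set or missing-data rule, and an unseen analysis plan may supply them. A reader might note that only the treatment arm has the daily listening, and assume unequal withdrawal and worse outcomes in leavers to reach a bias figure. Each input would be invented, so the article yields no such figure.
- *ANCOVA solves withdrawal.* Month-3 ANCOVA leaves out the same withdrawn patients as a month-3 t test does.

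The point cannot, however, be set aside as detail left to an analysis plan. The article names the between-group test outright and confines analysis of variance to within-group use.

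**Conclusion.** The concern holds as a recommended improvement; the planned test is not invalid. With 38 per group, baseline adjustment raises power from about 83% on final scores to 86%, 92% or 98% at correlations of 0.3, 0.5 or 0.7, and adds nothing at a correlation near 0. If change scores are what is meant, the t test has 69%, 83% and 96%, so at 0.3 it would miss the 80% target. These figures rest on the protocol's means and SDs, a two-sided test, equal SDs at baseline and end, and assumed correlations.

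The withdrawal advantage belongs to the mixed model, through the earlier scores of patients who leave later. It brings less bias only under missing at random; it does not cover withdrawal that depends on unobserved outcomes, and it cannot help for patients who leave before the first monthly visit. The size of any withdrawal bias cannot be derived from the article.

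**What to change.** In section 2.10, for VAS and THI scores only, replace the independent-samples t test with one of these:

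- **Preferred:** a mixed model for repeated measures on the scores at months 1, 2 and 3, with baseline score, arm, visit and arm-by-visit interaction. Include all randomised patients with at least one post-baseline score, in their assigned arm, and take the month-3 contrast between arms as the main estimate.
- **Simpler:** ANCOVA of the month-3 score on baseline score and arm. This gains the power in the table but does not use the earlier scores of patients who withdraw.

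Either option also settles whether final or change scores are compared. The chi-squared comparisons can stay as they are, and the sample size need not change. The cost is one revised paragraph and a little more analysis work in the software already named, with no new patients, visits or data.

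### The chi-squared test chosen for the THI grades and response categories is valid but ignores their order, and so gives up power; the response categories also overlap

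*Protocol article*

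**What the plan says.** Section 2.8 of the protocol defines the categories. For severity, "The THI scale is divided into 5 levels based on the total score", and "The higher the grade, the more serious the degree of tinnitus". For efficacy there are three outcomes, also built on the THI total:

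- "Cure: THI score dropped to less than 16 points"
- "Significantly effective: THI score decreased value ≥17 points"
- "Invalid: THI score decreased by <17 points, or even increased"

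Section 2.10 then assigns the tests. For categorical outcomes: "The Chi-Squared test is used for the composition ratio analysis of tinnitus severity and the difference in curative effect". No trend or ordinal version is named. The only rank method is kept for a different purpose: "rank sum test and analysis of variance are used for comparison within the group". Age, disease duration, THI and VAS scores and tinnitus loudness are measurement data, compared between groups by the independent-sample t test. The threshold is that P "is less than .05, the difference will be statistically significant"; sidedness is not stated.

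The sample size in section 2.3 (38 evaluable, 48 enrolled per group) rests on VAS. No power is claimed for the categorical comparisons.

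**The concern.** Pearson's chi-squared test on a table of two groups by five grades has 4 degrees of freedom, and on two groups by three responses it has 2. It asks whether the two distributions differ in any way. Shuffling the columns leaves the result unchanged.

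The trial asks something narrower: does adding acoustic therapy move patients towards milder grades and better responses? A test that uses the order spends 1 degree of freedom on that question. At stake is the chance that the categorical efficacy comparison comes out non-significant when a real, consistent improvement is present. Because the test is named, this is a stated choice and not detail left to an analysis plan.

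**Working it through.** **The plan's own figure.** Section 2.3 gives VAS means of 3.1 and 4.2 (difference 1.1) and SDs of 1.3 and 1.9. The root-mean-square SD is √((1.3² + 1.9²)/2) = 1.628. With two-sided 5% and 80% power, the printed formula gives 2 × (1.960 + 0.842)² × 1.628² / 1.1² = 34.4, so 35 per group; the t-based version gives 36. With SD 1.9 and a one-sided test, the formula gives 37 and the t-based version 38. The stated 38 is thus close to or equal to these results, depending on the convention. Dropout: 38/0.8 = 47.5, so 48. I use 38 per arm below.

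**Assumptions.** The protocol gives no category distributions, so these are mine: two-sided 5%, a common odds ratio of 2 to 3.5, and three control distributions per outcome.

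- Grades I to V: 20/20/20/20/20, 10/25/30/25/10 and 20/35/25/15/5%.
- Cure/Significantly effective/Invalid: 15/35/50, 10/40/50 and 5/35/60%.

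**Worked example, grades, odds ratio 3.** Control is 10/25/30/25/10%. Multiplying each cumulative odds by 3 gives cumulative proportions of 0.250, 0.618, 0.848 and 0.964, so the combination group is 25.0/36.8/23.0/11.6/3.6%. The chi-squared non-centrality is

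λ = n Σ (p − q)²/(p + q) = 38 × (0.0643 + 0.0224 + 0.0092 + 0.0486 + 0.0305) = 38 × 0.1750 = 6.65.

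On 4 df (critical value 9.49) this gives 52% power. The same λ on 1 df would give Φ(√6.65 − 1.96) = Φ(0.62), about 73%. Simulation of the rank-sum test gives 75%. The loss comes from spreading one directional signal over four degrees of freedom.

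**Worked example, response, odds ratio 3.** Control 15/35/50% becomes 34.6/40.4/25.0%, and λ = 38 × (0.0776 + 0.0038 + 0.0833) = 6.26. On 2 df (critical value 5.99) the approximate power is 60%; simulation gives 62% for chi-squared and 72% for rank-sum.

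**Range (20,000 simulated trials per scenario; range over the three control distributions):**

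| Outcome | Odds ratio | Chi-squared | Rank-sum |
|---|---|---|---|
| Five grades | 2 | 20–22% | 38–39% |
| Five grades | 3 | 50–53% | 74–76% |
| Five grades | 3.5 | 63–65% | 84–85% |
| Three responses | 2 | 26–28% | 34–36% |
| Three responses | 3 | 58–62% | 69–72% |
| Three responses | 3.5 | 70–74% | 80–82% |

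The linear trend test is close to rank-sum. With no treatment effect, the chi-squared test rejects in about 4 to 5% of trials. The pattern is the same at 48 per arm.

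**Cross-check with the plan's own effect size.** Taking 1.1/1.628 = 0.676 as a shift in an underlying normal score, the grades have 53–56% power with chi-squared and 77–79% with rank-sum or trend. The response categories have 61–64% and 71–74%.

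**A non-monotone case.** With 30/20/50% against 10/40/50%, chi-squared has about 62% power and rank-sum about 13%.

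**Do the response categories form a scale as written?** A patient whose THI falls from 24 to 14 ends below 16 (Cure) with a drop of 10 (Invalid). A patient who falls from 40 to 14 ends below 16 (Cure) with a drop of 26 (Significantly effective). Each fits two categories, so neither chi-squared nor a rank test can be applied until this is settled.

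**The case against.** The strongest reply is that nothing here is invalid. The chi-squared test holds its level, and direction is already tested: the grades and responses are coarsened THI scores, and THI and VAS scores are compared by t test. A t test at the VAS effect assumed in section 2.3 has about 83% power at 38 per arm. That stands. A reader might infer that the plan as a whole would miss a real improvement, that the trial is underpowered, or that false positives are inflated. The documents support none of these.

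Second, section 2.10 does not say whether the severity comparison is at baseline or after treatment, nor that all five grades or all three responses enter the table. Section 2.8 also gives a moderate-to-severe split at a THI of 38. At baseline, power is not the issue, and in a two-by-two table there is no order to ignore. This also stands and limits the point to post-treatment comparisons that keep three or more categories. Curative effect is post-treatment by definition, and section 2.8 gives it three levels.

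Third, the protocol states an order in words only for the grades. The response labels plainly run from best to worst, but their overlap has to be removed before that order can be used.

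Fourth, the change is not free, as the non-monotone case shows. That stands too, although a consistent shift is the effect this trial looks for.

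Small expected counts in the extreme grades are likely, but the handling of sparse tables is commonly left to an analysis plan, so I do not raise it.

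**Conclusion.** The point holds as a cheap improvement. The named test is valid but inefficient for ordered outcomes. Under a consistent shift at 38 per arm, the loss is about 16 to 24 percentage points for the five grades and about 8 to 11 for the three response categories. These sizes rest on assumed control distributions and odds ratios; the direction was the same in every monotone scenario tried. The larger loss belongs to the grades, where the timing of the comparison is unclear. The smaller one belongs to curative effect, which is the protocol's efficacy judgment. The VAS sample size and the t tests on THI and VAS scores are untouched. The overlap of the response categories is a contradiction within section 2.8 and must be resolved whichever test is used.

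**What to change.** 1. In section 2.8, reconcile the three response definitions so that each patient falls into exactly one category. The sponsor must decide, before the data are seen, how the overlapping cases are classed.
2. In section 2.10, say when the severity composition is compared. For post-treatment comparisons of grades and responses between groups, replace chi-squared with a Wilcoxon rank-sum or linear-by-linear trend test, or with a proportional-odds model reporting a common odds ratio and 95% confidence interval.
3. Keep chi-squared or Fisher's exact test for nominal characteristics.

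The cost is a few sentences, with no extra patients or data. The price is less power for a non-monotone difference and, if the model is chosen, the added assumption of proportional odds.

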## Abstract

**Background::**

There is no effective treatment for idiopathic tinnitus. Both acoustic therapy and acupuncture have been used in the treatment of idiopathic tinnitus, but the clinical efficacy is quite different. For there is no clinical study combining the 2, the purpose of this randomized controlled trial is to evaluate the effectiveness and safety of acoustic therapy combined with acupuncture in the treatment of idiopathic tinnitus.

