**Methods::**

This is a prospective randomized controlled trial to study the effectiveness and safety of acoustic therapy combined with acupuncture in the treatment of idiopathic tinnitus, and is approved by the clinical research ethics committee of our hospital. The patients are randomly divided into one of 2 treatment options: (A) acoustic therapy combined with acupuncture group and (B) simple acupuncture group. Patients, doctors, nurses, and data collection assistants are blinded to group allocation. Observation indicators include:

Data is analyzed using the statistical software package SPSS version 25.0 (Chicago, IL).

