Therefore, this protocol will combine acoustic therapy and acupuncture in the treatment of idiopathic tinnitus, and evaluate the effectiveness and safety of it.

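### Within-group tests share the P<.05 rule with no stated role, and the objective names the combination's effectiveness although the design identifies only what music adds to acupuncture

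*Protocol article*

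**What the plan says.** **Objective.** The Abstract (Background) says that "the purpose of this randomized controlled trial is to evaluate the effectiveness and safety of acoustic therapy combined with acupuncture" in idiopathic tinnitus. The end of section 1 repeats it: "this protocol will combine acoustic therapy and acupuncture in the treatment of idiopathic tinnitus, and evaluate the effectiveness and safety of it". The Abstract (Discussion) expects the results to supply evidence for using the combination.

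**Arms.** The Abstract (Methods) lists two: ("A) acoustic therapy combined with acupuncture group and (B) simple acupuncture group"). Section 2.7 adds: "The control group will be treated with acupuncture alone, and the treatment plan will be the same as that of the treatment group". No sham, untreated or music-only arm is described.

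**Analysis.** Section 2.10 plans two kinds of comparison.
- Between arms: "The independent sample *t* test is used for comparing the 2 groups", and "The Chi-Squared test is used for the composition ratio analysis of tinnitus severity and the difference in curative effect".
- Within arms: "the compatibility design data rank sum test and analysis of variance are used for comparison within the group".

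One rule closes the section: "If *P* is less than .05, the difference will be statistically significant". It does not separate the two kinds of test, and nothing calls the within-group tests descriptive or supportive.

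**Sample size.** Section 2.3 rests on the between-arm VAS difference, 3.1 (SD 1.3) against 4.2 (SD 1.9), and asks for 38 evaluable and 48 enrolled patients per arm.

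**The concern.** The objective names one quantity and the randomised contrast estimates another. Acupuncture is common to both arms and cancels in the comparison, leaving the increment due to music. The only planned analyses that touch the combination as a whole are the within-group tests, and these have no control for what would have happened anyway.

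The setting makes this more than a point of wording. The limitations in section 3 concede that full double-blinding is not attainable and that the outcomes are strongly subjective, so expectation can move the scores. Section 1 reports that systematic reviews leave the efficacy of acupuncture for tinnitus unsettled. The control arm therefore cannot serve as a proven treatment from which the total effect of the combination might be inferred.

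At stake is how the result may be reported. A significant fall in the combination arm, or a significant fall in one arm and not the other, would meet the protocol's only criterion for statistical significance and would fit the wording of the objective, yet neither would have randomised support.

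**Working it through.** **1. What the design identifies.** Write the mean change in each arm as a sum of parts: *c* for everything non-specific (natural course, regression to the mean, expectation), *a* for the specific effect of acupuncture, and *m* for whatever music adds on top of acupuncture.

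- Combination arm: *c + a + m*
- Acupuncture arm: *c + a*
- Between-arm difference: (*c + a + m*) − (*c + a*) = *m*
- Effect of the combination: *a + m*

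The randomised contrast gives *m*. The within-arm change in the combination arm gives *c + a + m*, from which *a + m* cannot be separated because no arm supplies *c* alone. The split treats *c* as equal in both arms; with no sham music, any extra expectation attached to the music falls into *m*.

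**2. The plan's own figure.** The sample size belongs to the between-arm contrast. The pooled SD is √((1.3² + 1.9²)/2) = √2.65 = 1.628 and the difference is 4.2 − 3.1 = 1.1. The printed formula, two-sided 5% and 80% power, gives 2 × (1.960 + 0.842)² × 2.65 / 1.1² = 34.4, so 35 per arm; the exact t calculation gives 36. The stated 38 is slightly larger, with power of about 0.83 by the t test. Allowing for withdrawal, 38/(1 − 0.20) = 47.5, so 48, as stated. Nothing in this point depends on the gap between 35 or 36 and 38.

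**3. How readily a within-arm test is significant when neither treatment works.** Set *a = m = 0* and let both arms fall by the same non-specific amount *c*. The falls and the SD of change are assumptions; the document gives neither. The range 1.3 to 1.9 borrows the score SDs of section 2.3. If the variance is the same at both times, an SD of change equal to the score SD implies a before–after correlation of 0.5, since SD × √(2(1 − 0.5)) = SD.

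For a paired t test with n = 38, the noncentrality is *c* / (SD/√38), with 37 degrees of freedom and a two-sided 5% critical value of 2.026. For *c* = 1.0 and SD = 1.9 it is 1.0 / (1.9/6.164) = 3.24, and the probability of a significant fall is 0.885.

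| Non-specific fall (VAS points) | SD of change 1.3 | 1.6 | 1.9 |
|---|---|---|---|
| 0.5 | 0.636 | 0.467 | 0.352 |
| 0.75 | 0.934 | 0.803 | 0.659 |
| 1.0 | 0.996 | 0.963 | 0.885 |

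**4. Significant in one arm only.** With independent arms and within-arm probability *p*, exactly one arm is significant with probability 2*p*(1 − *p*). For a common fall of 0.5 points this is 2 × 0.636 × 0.364 = 0.46 (SD 1.3), 2 × 0.467 × 0.533 = 0.50 (SD 1.6) and 2 × 0.352 × 0.648 = 0.46 (SD 1.9), although the arms do not differ.

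In all these cases *c* cancels from the between-arm difference, so the between-arm t test keeps its nominal 5% error rate.

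**The case against.** A reader might infer that the within-group tests are planned as evidence of efficacy. The document does not say so. Section 2.10 gives them no purpose, assigns the comparison of the two groups to the t test and the difference in curative effect to the chi-squared test, and section 2.3 sizes the trial on the between-arm VAS difference. The patient-level before–after definitions in section 2.8 can be compared between arms and do not make the within-group tests decisive. This objection stands.

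A reader might also infer that the objective claims effectiveness. It says evaluate, and the add-on structure is openly described. Comparing a combination with one of its components is a legitimate design. This stands too; what remains is that the wording is broader than the contrast.

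Two further inferences go too far. Monthly visits are in section 2.9, but section 2.10 does not say which visits enter the within-group tests, so it cannot be asserted that monthly scores are compared within arms. The lack of a joint longitudinal model is a detail that a condensed article may leave to the full protocol or analysis plan, and a between-arm t test on randomised groups is valid.

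Finally, the 89% is only the power of a paired test to detect a real average fall, which any trial would show, and the paired t test stands in for the rank test and analysis of variance that are named. That is fair. The figure shows how little a significant within-arm result says about treatment; it does not measure an error in the between-arm test.

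None of this answers the remaining point: the within-group tests are stated, they share the significance rule, they have no stated role, and the objective names an effect that the randomised comparison cannot deliver.

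**Conclusion.** The point holds as a mismatch of wording and role. The randomised comparison identifies the added effect of notched music over acupuncture alone, not the effectiveness of the combination. The within-group tests cannot fill that gap, and section 2.10 does not mark them as descriptive. The identification argument rests only on the arms described in the Abstract and section 2.7 and needs no outside figure.

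The size is illustrative. On an assumed SD of change of 1.9 and 38 patients, a non-specific fall of 1.0 VAS point gives a significant within-arm result about 89% of the time when neither treatment works, and 0.75 points about 66%. Over SDs of 1.3 to 1.9, a 1.0-point fall gives 0.89 to 0.996.

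The planned between-arm test is not invalidated, and the sample size is unaffected. The change should be made because it governs what the trial may conclude.

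**What to change.** - In the Abstract, section 1 and section 2.1, word the objective as the added effect of individualised notched music on top of acupuncture, compared with acupuncture alone. Bring the Abstract's statement of what the results will support into line, and use the same wording for the eventual conclusion.
- In section 2.10, report within-arm changes descriptively with confidence intervals, and remove the within-group significance tests as a basis for efficacy.
- State that efficacy is judged solely on the between-arm comparison already planned in section 2.10 and used for the sample size in section 2.3.

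The cost is a few sentences. Arms, visits and sample size do not change. The downside is a narrower claim: the trial could no longer be presented as showing that the combination as a whole works.
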